**Methods:**

This study will use both qualitative and quantitative methods to address important questions. Specifically, semistructured interviews using focus group and interview methodologies will be used to assess youths’ lived experiences and will account for specific details that quantitative methods may not be able to attain. In addition, quantitative methods will be used to examine direct and multilevel associations between neighborhood factors and youth substance use and mental health outcomes.

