Snowball sampling [55] is a recruitment technique in which research participants are asked to assist researchers in identifying other potential subjects. To justify the use of this technique, because we are seeking to collect data from participants who ideally would be *difficult* to reach through conventional and traditional methods of recruiting youth, snowball sampling is a useful technique for working with marginalized and hard-to-reach populations.

Venue-based sampling [51,52] is a recruitment strategy that entails targeted recruitment through preidentified venues in Paterson, New Jersey, where youth congregate. This sampling method will occur in 1 of 2 ways. The youth and community advisory board will be used as key informants to identify places where youth often congregate when they are not in school. We will outline 10-20 venues, and then the research team will visit those venues and attempt to recruit youth to participate in the brief survey. Youth will also have the opportunity to be a part of the qualitative part of the study at another time. In addition to venue-based sampling, participants will also be recruited through various sources, such as community partner organizations, through social media channels (Facebook, Twitter, and Instagram) and purposive and snowball sampling.

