#### Neighborhood Drug Availability

Neighborhood drug availability [64] will be measured using an adolescent report of 3 items. Adolescents indicate their agreement with each statement on a scale ranging from 1 (strongly disagree) to 5 (strongly agree). Example items include “Marijuana would be easy to find in my neighborhood,” “I know where to get drugs in my neighborhood,” and “Lots of drugs are sold in my neighborhood.” A mean score will be computed such that high scores indicate greater neighborhood drug availability.

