#### Neighborhood Resources

Neighborhood physical resources, such as libraries and parks, have been found to contribute to healthy development [64] and play a role in shaping observations and interactions with other residents. Four items asking about the availability or presence of (1) sidewalks or walking paths; (2) parks of playgrounds; (3) recreation, community center, or clubs; and (4) library or bookmobile will be used as indicators of the latent construct of neighborhood resources. Questions will be answered as no (0) or yes (1).

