#### Neighborhood Poverty

We will define neighborhood as a geographic unit and will measure it based on the census tract of residence. Census tracts commonly serve as proxies for neighborhoods and are often the basis for geographically delimited resource allocation. Census tract–level data will be acquired on the percentage of residents within each census tract that is at or below the poverty line. Furthermore, mean household income across the census tract will also be gathered as a continuous indicator of neighborhood-level income.

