#### Statistical Tests

Owing to the nature of the aims and the hypothesized outcomes, a more advanced and robust test of statistical relationships is needed for this study. SEM is a multivariate statistical analysis technique used to analyze structural relationships using a conceptual model, path diagram, and system of linked regression-style equations. SEM is the combination of factor analysis and multiple regression analysis and is used to capture complex and dynamic relationships between observed and unobserved variables [69,70]. SEM approaches are well-suited for this study because of their ability to deal with latent variables and the assessment of complex mediating relationships in causal analysis. On the basis of hypothesized model mentioned earlier, we predict that neighborhood characteristics will have a direct effect on youth substance use and depressive and anxiety symptoms. These effects will account for youth age (and possibly gender, race, and socioeconomic status). SEM is considered a confirmatory technique, as it extends the possibility of relationships among latent variables and includes 2 components: (1) a measurement model (eg, confirmatory factor analysis) and (2) a structural model. SEM allows the following: (1) more accurate estimates of the effects of hypothesized causal variables, (2) it allows the researcher to estimate all effects simultaneously, (3) greater accuracy of parameter estimates when examining competing models, and (4) it allows the researcher to compare the effects of multiple mediators. To use SEM, there are several assumptions that must be met: (1) a linear relationship is present between endogenous and exogenous variables; (2) there should be a cause-and-effect relationship between the endogenous and exogenous variables that are being tested based on theory; (3) data should be free of outliers because outliers can affect the significance of the model; and (4) there should be a nonspurious relationship between the endogenous and exogenous variables. Nonspurious relationships assume that the relationship between 2 variables cannot be explained without a third variable; (5) equations between variables must be greater than the estimated parameters; (6) a sample of at least 150-200 is preferred with at least 10-15 indicators; (7) error terms among endogenous variables and exogenous variables are assumed to be uncorrelated with other variable error terms; and (8) interval data are to be used for analysis [69,70].

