The last phase of the project includes a pilot feasibility trial of the adapted intervention among a sample of youth living in Paterson, New Jersey. During monthly meetings with youth and community advisory board members, research staff will discuss the use of evidence-based prevention interventions that address youth substance use and mental health. A specific strategy and an evidence-based intervention (eg, Substance Abuse and Mental Health Services Administration’s National Registry of Evidence-based Programs and Practices) will be decided through findings collected from venue-based sampling methods and suggestions from the youth and community advisory board. Participants will be recruited from partnering youth organizations to participate in the intervention. We will pilot-test the intervention with a group of youths who are similar developmentally by age, race, ethnicity, and gender. Youth will be sampled from schools and youth-serving organizations across all 6 wards. Although interventions have the power to increase perception, increase knowledge about substances, and reduce risky behaviors, we understand that youth are nested in their environments. Therefore, we are cautious of being ambitious in our goals, as changes cannot occur if the community norms remain the same. Consequently, we will meet the youth and community advisory board to decipher the most effective mode of intervention that can occur at the individual and community levels. We intend to pilot a combination of effective strategies (eg, prevention education, case management, and referral to therapy). We will first identify and adapt an evidence-based intervention that will incorporate elements of mental health discussions, substance use, and refusal strategies, as these have proven to be the most effective among ethnic minority youth. In addition, and most importantly, the intervention will be informed by findings from participants and youth and community advisory board discussions. Although we discussed earlier the flaws in primarily recruiting and working with youth in schools only, the priority will be to adapt an existing prevention intervention to be feasible for youth who are in school and other youth who are not engaged in school. We hypothesize that unique developmental, cultural, racial, and gender-specific differences will arise and inform how to adequately decide, adapt, and deliver an effective prevention intervention for Paterson youth.

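### The abstract promises multilevel neighborhood associations, but the analysis and power sections give no tract or cluster term, which leaves the census-tract poverty and income paths with understated standard errors if run as written

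*Protocol article*

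**What the plan says.** The Abstract (Methods) says that "quantitative methods will be used to examine direct and multilevel associations between neighborhood factors and youth substance use and mental health outcomes". The Neighborhood Poverty measure fixes the unit: "We will define neighborhood as a geographic unit and will measure it based on the census tract of residence". It then adds that "Census tract–level data will be acquired on the percentage of residents within each census tract that is at or below the poverty line", and that mean household income will be gathered for the same tracts. All youths living in one tract therefore share the same value of both variables.

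The other neighborhood measures differ in kind. Drug availability "will be measured using an adolescent report of 3 items". Four yes/no answers from each youth "will be used as indicators of the latent construct of neighborhood resources", and safety rests on two items that each youth answers. These vary between youths in the same tract.

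Under Statistical Tests, the hypothesis is "we predict that neighborhood characteristics will have a direct effect on youth substance use and depressive and anxiety symptoms", to be tested by SEM accounting for age and possibly gender, race and socioeconomic status. No tract term, random effect, site term or clustered standard error is named there or elsewhere in the quantitative analysis plan. The robust analyses mentioned under Outliers concern outliers. The Statistical Power section gives three examples (SEM fit, multiple regression, logistic regression) and sets a target of 720, with no ICC, design effect or number of tracts.

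On recruitment, Participant Recruitment and Sample Size states "We will outline 10-20 venues, and then the research team will visit those venues". The same section adds partner organizations, social media, purposive and snowball sampling.

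**The concern.** The Abstract announces one kind of analysis, while the sections that should deliver it describe and power something less. For a predictor that is constant within tract, the information comes mainly from the number of tracts. Recruiting more youths into the same tracts helps little once outcomes correlate within tract. An SEM that treats youths as independent would report standard errors for the poverty and income paths that are too small, and hence too many significant results.

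These findings are among the inputs to the choice and adaptation of the prevention program. A spurious or falsely precise tract effect could therefore influence that step.

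**Working it through.** **1. The plan's own power figures.** Alpha is not stated; two-sided 0.05 is assumed.

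- Logistic: n = (1.960 + 0.842)² / [p(1−p) × (ln OR)² × (1−R²)], with p = 0.40, OR = 1.75 and R = 0.30. This gives 7.849 / (0.24 × 0.3132 × 0.91) = 114.8, so 115, as stated.
- Regression: f² = 0.05/0.75 = 0.0667. The normal approximation gives 7.849/0.0667 = 118 and the exact noncentral F gives 120. Power at 115 is 0.784, close to the stated 0.80 at about 115.
- SEM: 96% at N = 300 and 20 df is reproduced for a root mean square error of approximation (RMSEA) of 0.05 against 0.10 (0.96).

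All three figures come from formulas for independent observations.

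**2. Effect of clustering on a tract-level path.** N = 720 comes from the protocol. The number of tracts J (20 to 40) and the within-tract ICC (0.01 to 0.10) are assumptions. With equal tract sizes m = 720/J, the design effect is DE = 1 + (m − 1) × ICC. The true standard error is √DE times the one reported under independence, so a nominal 5% test has actual size 2 × [1 − Φ(1.96/√DE)].

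Example with J = 30, m = 24, ICC = 0.02: DE = 1 + 23 × 0.02 = 1.46, √DE = 1.21, 1.96/1.21 = 1.62, size 10.5%.

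A simulation with 4,000 data sets per cell and no covariates checks this. It also covers a predictor that varies within tract and has its own ICC of 0.10, standing in for a self-report measure.

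| Tracts (youths each) | ICC | DE | √DE | Size, closed form | Simulated, tract-level predictor | Simulated, self-report predictor |
|---|---|---|---|---|---|---|
| 20 (36) | 0.01 | 1.35 | 1.16 | 9.2% | 8.5% | 5.7% |
| 20 | 0.02 | 1.70 | 1.30 | 13.3% | 13.2% | 6.4% |
| 20 | 0.05 | 2.75 | 1.66 | 23.7% | 22.9% | 6.5% |
| 20 | 0.10 | 4.50 | 2.12 | 35.6% | 35.7% | 8.9% |
| 30 (24) | 0.01 | 1.23 | 1.11 | 7.7% | 7.1% | 5.6% |
| 30 | 0.02 | 1.46 | 1.21 | 10.5% | 10.6% | 6.1% |
| 30 | 0.05 | 2.15 | 1.47 | 18.1% | 17.6% | 6.6% |
| 30 | 0.10 | 3.30 | 1.82 | 28.1% | 27.1% | 7.6% |
| 40 (18) | 0.01 | 1.17 | 1.08 | 7.0% | 6.8% | 6.0% |
| 40 | 0.02 | 1.34 | 1.16 | 9.0% | 8.8% | 5.5% |
| 40 | 0.05 | 1.85 | 1.36 | 15.0% | 15.4% | 5.9% |
| 40 | 0.10 | 2.70 | 1.64 | 23.3% | 22.9% | 6.6% |

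The closed form and the simulation agree. The inflation is large for tract-level predictors and slight for self-reports.

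**3. Effective sample size.** 720/DE ranges from 615 (40 tracts, ICC 0.01) to 160 (20 tracts, ICC 0.10), always above the 115 of the regression and logistic examples. This is optimistic for tract-level paths because it ignores the limited degrees of freedom from few tracts. In addition, a predictor constant within tract can by itself account only for between-tract variance. The regression example's 5% therefore fits such a predictor only if at least about 5% of outcome variance lies between tracts.

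**4. Venues.** If all 720 came from 10 to 20 venues (72 to 36 each), DE would be 1.70 to 2.42 at ICC 0.02 and 2.75 to 4.55 at ICC 0.05. Effective N would be 424 to 298 and 262 to 158. This is an upper-end case, because venues are only one recruitment route.

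**The case against.** The strongest reply is that this is a condensed article: the Statistical Tests section is a general account of SEM, the Abstract points towards multilevel modelling, and the handling of clustered standard errors is commonly left to an analysis plan that is not shown. Part of this stands. A reader might infer that the protocol commits to a single-level SEM, but it never says so. The listed assumption of uncorrelated errors concerns error terms of variables, not of youths, so it does not settle the matter. What remains is a mismatch inside the document: a multilevel promise that the analysis section does not specify and the power section does not reflect.

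Four other stronger readings also go too far:

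- **All neighborhood paths are badly affected.** Only poverty and income are constant within tract. Drug availability, resources and safety are individual answers, with slight inflation.
- **The sample consists of 10 to 20 venue clusters.** Schools, youth organizations, social media and snowball referral also contribute. They bring dependence of their own, but its size cannot be derived from the document.
- **The study loses its stated power.** The effects in the examples that need about 115 mostly remain detectable with 720 youths.
- **The protocol concedes statistical dependence.** The remark "we understand that youth are nested in their environments" in the Discussion explains why the goals of the intervention are modest. It is not about standard errors.

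It is also fair that program choice depends on advisory-board and community input as well as on these models.

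**Conclusion.** The point holds for the tract-level poverty and income paths and for the mismatch between the Abstract and the Statistical Power and Statistical Tests sections. If the SEM is run as described, with nothing added for tract, a nominal 5% test of those paths has a type I error of about 7-9% at ICC 0.01, 9-13% at 0.02 and 15-24% at 0.05. This rests on an assumed 20 to 40 tracts of equal size, on the assumed ICCs, and on a simulation without covariates; adjustment could lower the residual ICC. With no within-tract correlation there would be no inflation. For the self-reported measures the figure is about 6-9% over outcome ICCs of 0.01 to 0.10, given a predictor ICC of 0.10. Dependence within venues or partner sites adds an amount that cannot be quantified from the document. The harm is false positives and false precision on tract-level paths rather than lost power for the stated examples.

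**What to change.** - **Statistical Tests:** state that models with tract-level predictors will be two-level (youth within tract) or will use standard errors clustered on tract, with a small-sample correction for the number of tracts. This also brings the section into line with the Abstract.
- **Data collection:** record each youth's census tract and recruitment site or channel. Adjust for channel or check sensitivity to it. Venue alone cannot serve as the cluster, because many youths will be recruited elsewhere.
- **Statistical Power:** restate power for the tract-level paths with an assumed ICC and the expected number of tracts. Keep the existing examples for individual-level predictors only.

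The cost is a few sentences of wording and two identifiers kept with the survey record. The channel should be captured at collection, since it may not be recoverable later. Intervals for the tract-level paths will be wider and the power statement less favourable.

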### Youth Substance Use and Mental Health Trends in Paterson, New Jersey

Local-level data collected by a coalition in Paterson, New Jersey, found that 1 in 4 youth in Paterson used marijuana in the past 30 days [39], indicating that marijuana is the most widely used substance among the youths, followed by alcohol. Compared with other residents in Passaic County, Paterson residents have higher access to alcohol because of the high number of alcohol outlets in the city [39]. Thus, Paterson is a unique city to investigate and uses venue-based sampling techniques for this study because of the following reasons: (1) significant representation of the 2 largest ethnic groups in the nation (Black and Hispanic) that reside in Paterson and (2) the city’s wide availability of licit and illicit drugs that may impact community norms and values. For example, based on the parameters set by the New Jersey Division of Alcoholic Beverage Control [40], the city of Paterson with more than 147,000 residents should not exceed a total of 49 consumption licenses, including restaurants and bars, and 19 off-premises licenses, including liquor stores and bodegas. However, Paterson is only 8.4 square miles and has more than 200 alcohol outlets—4 times the legal limit because of grandfather clauses [37]. Alcohol outlet density is not only associated with increased crime, violence, and heavy alcohol and drug use but also provides Paterson youth with greater access to alcohol, leading to an increased probability of underage drinking [41-43]. Among Paterson youth aged between 13 and 18 years, 30% of youth reported that they had used alcohol before the age of 13 years [39]. Local-level data show that Paterson youth who drank alcohol during the past 30 days were also 3 times more likely to smoke marijuana before the age of 14 years [39]. Of note, 60% of Paterson youth reported purchasing alcohol from liquor stores and 40% of Paterson youth admitted to having an adult purchase alcohol from liquor stores for them [39]. Furthermore, Black (33.3%) and Hispanic (29.7%) Paterson youth reported the highest marijuana use before the age of 13 years [39]. In addition, the city is currently facing an extreme opioid crisis, with Paterson being ranked the second city in New Jersey for the highest rate of heroin abuse [44]. Among Paterson youth, 6.2% reported using cocaine and 6.8% reported using heroin; these rates are higher than the state averages [39]. These findings highlight the need to address substance use among Paterson youth, specifically, investigating antecedents and correlates to inform interventions to reduce substance use among youth. Although empirical studies suggest a bidirectional relationship between substance use and mental health [41], it is important to acknowledge that they are correlated and may influence each other, leading to poorer short- and long-term outcomes. Indeed, among Paterson youth sampled, there is a high mental health burden, as 50% of youth reported experiencing depressive symptoms and 57% reported experiencing anxiety symptoms [39]. Overall, 70% of youth who used either alcohol or marijuana in the past 30 days reported experiencing greater symptoms of anxiety and depression [39]. Given that both depression or anxiety symptoms and substance use are correlated and are associated with other negative health outcomes [45,46], it is important to understand these associations to inform and improve interventions aimed at decreasing mental health disparities and limiting substance use.

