#### Statistical Power

In general, statistical power should be adequate. An SEM model with a degree of freedom as low as 20 and a sample size of 300 will have 96% power to build a good-fit model (ie, root mean square error<0.05) [69,70]. With the target sample size (N=720), the study will easily have more df and will achieve higher power to build and test the proposed SEM models. For a multiple regression equation with 5 predictors where the squared multiple correlation is 0.25 and where one wants to detect a predictor that accounts for at least 5% unique variance in the outcome, the required sample size to achieve a power of 0.80 is approximately 115 [68]. As another example, for a logistic regression analysis in which the target predictor is a continuous predictor with 5 other predictors in the equation where the event rate at the mean of all predictors is 0.40 and where the multiple correlation of the predictor with the other predictors is 0.30, the sample size needed to detect an odds ratio (applied to standardized metrics) of 1.75 is 115 [68].

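### Uncorrelated error terms are listed as something SEM requires; SEM does not require them, and the rule sits badly with outcomes the protocol describes as correlated

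*Protocol article*

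**What the plan says.** The Statistical Tests section of the protocol article introduces a numbered list with the words "To use SEM, there are several assumptions that must be met". Item 7 is that "error terms among endogenous variables and exogenous variables are assumed to be uncorrelated with other variable error terms".

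The same section states one structural prediction, that "neighborhood characteristics will have a direct effect on youth substance use and depressive and anxiety symptoms", adjusted for age and possibly for gender, race and socioeconomic status. It names no path or covariance among the outcomes. It does give "the assessment of complex mediating relationships in causal analysis" as one reason for choosing SEM.

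The section on youth substance use and mental health trends says that "empirical studies suggest a bidirectional relationship between substance use and mental health" and that "it is important to acknowledge that they are correlated and may influence each other". It gives no coefficient.

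The Statistical Power section cites a df as low as 20 and a sample of 300 as giving 96% power to "build a good-fit model (ie, root mean square error<0.05", and says that the target of 720 will come with more df. Under Depressive and Anxiety Symptoms, both symptom scales are six-item sets from one inventory, with the same one-week recall and the same response scale.

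**The concern.** Uncorrelated error terms are a modeling choice in SEM, yet item 7 presents them as a precondition. Applied to three outcomes that each depend directly on neighborhood characteristics, the rule says that the outcomes are unrelated once neighborhood and covariates are accounted for. The protocol's own background makes that doubtful for substance use and mental health. Two symptom scales from one inventory make it doubtful for depression and anxiety as well, although that second point is an inference from the measures and not something the protocol states.

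Two things are at stake. A false zero restriction produces misfit that has nothing to do with the neighborhood hypothesis, and could lead to the model being altered after the data are seen. It also removes the sampling covariance between path estimates for different outcomes, so any comparison of those paths uses the wrong standard error. The single-outcome path estimates, which carry the stated hypothesis, are little affected when all outcomes share the same predictors.

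**Working it through.** **Inputs from the protocol article.** df 20, N 300, power 96%, fit benchmark 0.05 (read as RMSEA) and target N 720, all from Statistical Power. From the trends section: depressive symptoms 50%, anxiety symptoms 57%, greater symptoms among past-30-day users of alcohol or marijuana 70%, and marijuana use in the past 30 days 1 in 4.

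**The plan's own figure.** With noncentrality (N − 1) × df × RMSEA² and alpha 0.05 (assumed), N 300 and df 20 give 95.9% power for RMSEA 0.05 against 0.10. So 96% is reproduced under that contrast, which the article does not state.

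**One omitted residual correlation r, rest of the model correct.** The population misfit is F0 = −ln(1 − r²), RMSEA = √(F0/df), and the rise in chi-square is about 720 × F0.
- Threshold at df 20: r = √(1 − e^(−20 × 0.05²)) = √(1 − e^(−0.05)) = 0.221.
- r = 0.30: F0 = 0.0943, chi-square about 68, RMSEA = √(0.0943/20) = 0.069.
- r = 0.60: F0 = 0.4463, chi-square about 321, RMSEA 0.149.
- The threshold rises with df: 0.35 at df 51, 0.47 at df 100, 0.58 at df 167.

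**Three equal omitted residual correlations ρ.** F0 = −ln[(1 − ρ)²(1 + 2ρ)].

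| ρ | RMSEA at df 20 | Chance that sample RMSEA < 0.05, N 720 |
|---|---|---|
| 0.1 | 0.038 | 91% |
| 0.2 | 0.074 | 0.5% |
| 0.3 | 0.110 | about 0% |

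The threshold ρ is 0.13 at df 20, 0.21 at df 50, 0.30 at df 100 and 0.43 at df 200. With the three covariances freed and the rest of the model correct, df is 20 − 3 = 17, and the chance of a sample RMSEA below 0.05 is 97.1% at N 300 and above 99.9% at N 720.

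**Latent outcomes** (loadings 0.7, assumed; fitted numerically).
- Two 6-item factors forced to be uncorrelated (df 54): true factor correlations of 0.3, 0.5, 0.6 and 0.7 give RMSEA 0.035, 0.061, 0.075 and 0.090.
- Three latent outcomes with neighborhood effects of 0.2 to 0.3 (assumed): 0.05 is reached at a residual correlation of about 0.3 with df 51. With df 167 (6 + 6 symptom, 5 use and 3 neighborhood items) it takes about 0.5, and a value of 0.3 gives only 0.030 to 0.031.

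**Rough size of the association.** Assume that a share u of 25% to 40% are users and that the 70% is comparable with the overall symptom rate s. Then phi = u(0.70 − s)/√[u(1 − u)s(1 − s)].
- s = 0.50: 0.23 at u = 0.25 and 0.33 at u = 0.40.
- s = 0.57: 0.15 at u = 0.25 and 0.21 at u = 0.40.

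Shared neighborhood effects of 0.2 to 0.3 account for only 0.2² = 0.04 to 0.3² = 0.09 of this.

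**Comparing paths across outcomes.** With the same predictors and equal path variances V, the variance of a difference between two paths is 2V(1 − ρ). The restricted model reports 2V. At ρ = 0.3 the reported standard error is too large by 1/√0.7 = 1.20, or about 20%.

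**The case against.** The strongest reply is that correlated variables are not correlated error terms. Shared predictors or a path between outcomes could carry the association, and the plan leaves mediation open. That stands: a reader might infer that the protocol imposes a restriction it elsewhere calls false, but the passages are in tension and do not strictly contradict each other. Two things weaken the reply. The only prediction stated has parallel effects, and a one-way path would have to choose a direction where the background describes the relationship as running both ways.

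A second reply is that the list is generic, and that the full model, with its fixed and free parameters, may sit in a document not shown. It is true that no path diagram or parameter list is given, and that absence is no fault. But item 7 is a stated rule introduced as mandatory, and read literally it excludes the free covariances that a fuller plan might want.

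A reader might also infer that the study has set RMSEA below 0.05 as its success criterion and will miss it. The documents do not support this. The value describes a good-fit model inside a power statement, no acceptance rule is given, and df 20 is a floor that the authors expect to exceed. With item-level measurement, moderate residual correlations still meet 0.05.

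Finally, the stated hypothesis concerns single-outcome paths, and no test comparing paths across outcomes is announced. That also stands, and it limits the harm.

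**Conclusion.** The point holds in a limited form. Item 7 calls something a requirement of SEM that is not one, and it fits poorly with the stated parallel structure and with the protocol's account of substance use and mental health. If neither shared predictors nor a directed path carry the association, the zero restriction is a misspecification. Whether it shows in RMSEA depends on residual correlations and df that the documents do not give. It can at the df 20 floor, and need not at item-level df. A high df dilutes the misfit in RMSEA without removing it, so standard errors for cross-outcome comparisons would still be wrong.

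The sizes above assume that the rest of the model is correct. The latent results also assume the loadings and neighborhood effects, and the rough phi of 0.15 to 0.33 rests on an assumed share of users and on comparability of the symptom percentages.

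**What to change.** Reword item 7 so that error terms are assumed uncorrelated with the exogenous predictors. Add that residual covariances among substance use, depressive symptoms and anxiety symptoms are freely estimated for every pair not already joined by a directed (mediating) path. The exception matters because a path and a residual covariance for the same pair are generally not identified together without further restrictions.

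The cost is a sentence or two and at most three df. The Results section describes the study as still in planning, with recruitment yet to begin, so the change can be made before any data are seen.
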